### Randomization procedure

Randomization will occur at the level of the Community Healthcare Centers. Four Centers (20 clinic sites) will be randomized to receive the intervention and four centers (20 clinic sites) will be randomized to the control condition. To minimize potential imbalance in randomization, we will employ a multivariable score based pair-wise matching method [23] to achieve the optimal balance by location, size, population covered, HbA1c level, and other characteristics of recruited patients including age, gender, insurance status, insulin status, and body weight. We will first weigh covariates according to relevance of potential bias introduced, and then compute a multivariable score using an established algorithm after data are standardized and appropriately weighted. We will then identify four matched pairs, with each pair consisting of two facilities with closest multivariable scores. Randomization will be performed within each pair, with one Center randomized to receive the intervention, and the other to the control condition. This process will be repeated to obtain all possible pair-wise combinations for randomization. We will then assess balance for each covariate as a proportion of imbalance detected over all combinations. When balance is not ideal, the process will be repeated after adjusting the weighting system. After an appropriate weighting scheme is determined, the centers will be paired and a final randomization will be performed. This procedure will ensure more comparable patient populations with respect to clinic characteristics. Randomization at the Center level will help avoid contamination issues at the healthcare provider level.

### Usual care

In the control arm, usual diabetes care will continue according to current national guidelines: conventional clinical consultations, treatment provision according to existing knowledge and at the individual clinician’s discretion, no training in communication skills, and no literacy-/numeracy-sensitive Diabetes Education Toolkit materials.

The control sites will receive a program designed to educate healthcare providers about diabetes care based on the latest diabetes management recommendations and educational materials from the Chinese Guideline for Diabetes Care and Education, which will help to control for Hawthorne effects that might result in improved care.

### Intervention

The intervention will include two main components: i) the Partnership to Improve Diabetes Education Toolkit (PRIDE), a set of plain-language tools to aid provider-patient communication about diabetes management, and ii) a Clear Health Communication Curriculum, a structured training program for healthcare providers to improve diabetes-related counseling communication skills, with specific attention to issues of literacy and numeracy.

#### Diabetes education toolkit (PRIDE)

The PRIDE toolkit will consist of a host of educational materials that have been designed specifically to improve patient understanding and self-management behaviors in patients with lower literacy or numeracy skills. The PRIDE toolkit will be based on the Diabetes Literacy and Numeracy Education Toolkit developed and validated previously [24].

The materials in the PRIDE toolkit are designed specifically to help educate diabetes patients about self-management skills, with 24 educational modules covering all components of diabetes self-management including diet, exercise, foot care, glucose monitoring, and medication management, and enhanced diabetes log sheets that can be shared with patients to help improve their self-management. The modules are written at a low literacy level with many pictures, white space, and other accommodations for low literacy patients. Sample numeracy-oriented accommodations include color coding to help with number hierarchy, the use of insulin pens or syringes with colored marks to aid patients with difficulty measuring insulin, the use of tables and sentences to simplify medication instructions, and simplifying instructions by providing more basic alternatives that do not need as many math skills (e.g., a “plate method” or color coded scoop method instead of carbohydrate counting). For tasks that require math skills, worksheets are provided for patients to practice skills to help gain proficiency.

The toolkit is designed to help accommodate patients of all literacy levels, particularly those with poor literacy or numeracy skills. The PRIDE toolkit also acts as a disease management intervention at the provider and system level by i) acting as a “reminder” system to providers about certain treatment goals, ii) providing a structured approach to addressing self-management goals, including “care algorithms” that promote more systematic approaches to care, and iii) materials addressing important socioeconomic and community level barriers that can impede diabetes care.

Providers in the intervention Centers will be trained in the proper use of the PRIDE toolkit materials and will be expected to use the materials during regular patient-related visits. At each visit, providers will be asked to cover at least two components from the toolkit materials, and to perform and document at least one goal-setting task with the patient. They will share components of the toolkit directly with the patients for the patients to use and take home with them. Providers will be expected to spend approximately 5 to 7 minutes per visit using the toolkit materials with the patients. We anticipate that visits will occur at least every 3 months, in accordance with American Diabetes Association guidelines for diabetes follow-up, or more frequent, as needed. Paper printouts of toolkit materials will be made available in central locations in the intervention Centers for easy access.

#### Clear health communication curriculum for health care providers

Healthcare providers in the intervention arm will be trained in improved health communication skills with a specific emphasis on improving communication to aid patients with poor literacy or numeracy skills. All intervention clinic health care providers (physicians, nurse practitioners, registered nurses, dieticians, and health educators) will gather to obtain an approximately 5 to 6 hour training before the initiation of the intervention. The on-site training of the healthcare providers is essential to promote intervention fidelity and allow rigorous evaluation of the impact of the intervention. To promote provider participation, we will provide certificates with scores of Continuing Medical Education to all providers that participate in the training; we will also provide other nominal incentives for participation (free educational materials, food, pens, etc.).

During the training session, the healthcare providers will receive informational and hands-on training in the following areas: i) diabetes management, ii) introduction to the diabetes education toolkit, iii) clear health communication skills, and iv) application of the diabetes education toolkit using principles of clear health communication.

All intervention health care providers will undergo a post-training certification process to ensure that they have learned the materials. Healthcare providers will meet certification if they accomplish >90% of items listed on a Health Care Provider Certification Checklist at the end of the training day. Providers who fail this certification process will need to participate in additional 1:1 training with the research team until they meet adequate certification criteria. If a provider cannot meet certification requirements, then the participating Center will need to identify additional health care providers to participate in the study.

### Data collection procedures

#### Baseline survey

We will collect baseline characteristics related to the patients and the healthcare providers, which include the following variables:

*Patients*: Age at study entry, gender, date of birth, number of years living in Shanghai, household composition (number of children, marital status, etc.), Mandarin proficiency, health insurance status, employment, income level, years of education, lifestyle (smoking status, dietary habits, and physical activity), literacy level (as measured by the validated Chinese versions of Health Literacy Management Scale) [25], diabetes-related numeracy (as measured by the C-DNT-5), and measures related to clinical history, including years of diabetes, current diabetes medications, history of diabetes education, and glucose monitoring frequency.

*Healthcare Providers*: age, gender, years of education, type of provider (physician, nurse, dietician), Certified Diabetes Educator Status (Yes or No), and satisfaction for health care.

#### Collection of measures

HbA1c and lipids tests will be performed throughout the study using Point-of-Care Equipment available in each Community Health Center (high-performance liquid chromatography for HbA1c, and Automatic Analyzer for Lipids). Self-management activities will be assessed using the previously validated Chinese version of Summary of Diabetes Self-Care Activities [26]. Self-efficacy will be assessed using a scale validated in Chinese adults [26, 27].

The majority of measures will be collected at baseline and 3, 6, 12, and 24 months. The schedule for data collection is summarized in Table 1.

**Table 1 Tab1:** **Study schedule for data collection**

	Baseline visit	3 month visit	6 month visit	12 month visit	24 month visit
**Patients**					
Characteristics	X				
Health literacy/numeracy	X				
HbA1c tests	X	X	X	X	X
Lipid tests	X			X	X
Systolic and diastolic blood pressure	X	X	X	X	X
Self-management behaviors	X		X	X	X
Self-efficacy	X		X	X	X
**Healthcare Providers**					
Characteristics	X				
Satisfaction with visits	X		X	X	X
Use of intervention (Toolkit) or control (Chinese Guideline for Diabetes Care and Education) materials*	X	X	X	X	X
Certification of training	X	X	X	X	X

*Intervention providers will document after each visit what components of the Diabetes Education Toolkit they used. Control providers will document what Chinese Guideline for Diabetes Care and Education materials they used.

#### Related cost

Fixed and variable costs of the intervention program will be estimated, as well as the short-term and long-term cost-effectiveness of the program. The intervention costs will be subdivided into four categories of costs:i.*Implementation fixed costs* will include all labor, supply, and space costs of initiating and running the program that are independent of the number of participants in the program. These costs include the cost for program site personnel to attend training sessions before initiation of the program as well as during the program, and the cost of setting up a system to run the program from the clinic site.ii.*Implementation variable costs* will include all labor, supply, and space costs of running the program that are dependent on the number of program participants. These costs include printing costs for educational materials, labor costs for educating and monitoring the patients, and space costs for storing materials and meeting with patients. All program-related activities that occur within a 2-week time window will be timed using stop watches. These activities will include preparation for the patients’ clinic visits (including gathering educational materials), the clinical encounter, follow-up telephone calls with the patients, and documentation of the visit. These activities will be timed for both the intervention and the control group Centers. The labor cost will be estimated according to the individual’s salary level. Supply and space use for each program activity will also be determined. Costs will be applied to the supplies used based on wholesale acquisition costs. Costs will be applied to clinic visit and storage space used based on standard space overhead rates applied at the program sites. Variation in the fixed and variable implementation costs across the different program sites will be reported.iii.*Disease*-*related costs* will be derived from health service use data collected during the trial. This will include outpatient drugs prescribed including the dose and duration of therapy, physician visits, laboratory tests, emergency room visits, and hospitalizations. Standard charge will be used to estimate the unit costs for each type of health service, including the medical chart review and extracting, medical insurance system query, and the Physician’s Fee Reference for any healthcare provider costs.iv.*Patient*-*related costs*, including travel time and costs, total time in the clinic (including time to register, to wait to be seen, to meet with the providers, and to check-out of the clinic), and other incidental costs for each physician and emergency room visit, will be measured using a patient survey administered to all patients visiting the physician or emergency room during the 2-week time window in which the study is being completed. In sensitivity analyses, disability-related costs related to lost work will also be included.

Program development- and research-related costs will not be estimated since they are one-time only costs and would not be incurred when using the program materials in other populations after the end of the study.

### Quality control

A local project office will be set up in each Community Healthcare Center to monitor patient recruitment, consent, and collection of measures. One project officer at each Center will be trained in the recruitment of all patients, including those with lower literacy skills. This process will be rigorously overseen by the Principal Investigator and research team. In addition, the Study Project Coordinator at Fudan University will provide oversight over the project officers. All data will be key-entered in Fudan University.

### Statistical analyses

Comparison of participants by intervention and literacy status will be conducted using χ^2^ tests (for categorical variables) and *t*-tests or Wilcoxon rank-sum tests (for continuous variables). Analysis of covariance will be used to evaluate the improvement in HbA1c levels after adjusting for baseline values. Multivariable general linear models will be used to additionally adjust for other baseline covariates including age, sex, and diagnosis date. Two types of cost-effectiveness ratio (CEA) will be performed: i) a short-term 1-year CEA using a surrogate clinical endpoint, HbA1c, and ii) a long-term lifetime CEA with the outcome measure of quality-adjusted life-years gained. The short-term CEA will use the results of the 1-year cost and clinical analyses to compute the cost-effectiveness ratio, incremental cost per additional person with a reduction of >1% in HbA1c level. The 95% confidence limits for the cost and clinical outcomes measures will be used as input parameter value ranges tested in one-way sensitivity analyses. The long-term CEA will be performed using the Center for Disease Control Diabetes Cost-Effectiveness Group Model that evaluates the cost-effectiveness of intensive glycemic control, blood pressure control, and cholesterol control in people with diabetes [28]. All analyses will be performed using SAS version 9.13.

Approval was obtained from the Medical Ethics Committee of School of Public Health, Fudan University (IRB00002408 & FWA00002399) (registration number: 2013-06-0451). The involved local medical ethics committees in the Center for Disease Control and Prevention of Changning District and the Center for Disease Control and Prevention of Minhang District agreed with this approval.

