**Flowchart of the study.**

### Setting

A total of 800 diabetes patients will be recruited from eight Community Healthcare Centers in Minhang and Changning district of Shanghai, China. Five clinic sites will be selected from each Center. All clinic sites meet the following criteria: i) at least 20 patients can be recruited per site; ii) at least 2 to 4 physician(s), nurse practitioner(s), or diabetes educator(s) per Center can participate in the intervention; iii) the site agrees to participate for a minimum of 2 years; and iv) the site agrees to be randomized to either arm of the study.

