A possible limitation of the study is the short 1-year intervention, which may not be long enough to observe the effect of the intervention on occurrence of diabetes complications. In this study, the main outcome is the reduction in HbA1c level, which is a surrogate marker for long-term outcomes. Studies such as the DCCT and the UKPDS demonstrate that reducing HbA1c by ~0.7% can reduce micro-vascular complications by as much as 40 to 60%. Lowering HbA1c in T2DM also can decrease the absolute risk of developing coronary heart disease by 5 to 17% and all-cause mortality by 6 to 15% [29]. We can assume that if 1-year intervention can decrease HbA1c level significantly, it will improve long-term outcomes of diabetes patients. We also include blood pressure and lipid control as clinical outcomes. Second, the 1-year intervention may lead to a high drop-out rate. To prevent drop-out, local research assistants/nurses will help patients to complete the questionnaires and will make appointments for follow-up assessment. Long-term incentives will also be applied for both the healthcare providers and the patients. Third, although all Community Healthcare Centers in Shanghai provide diabetes care services according to the Guideline of Chinese Diabetes Prevention and Control, the usual care in the Centers of Minhang district is somewhat different from that in Changning district. In order to overcome this limitation, we will ensure the matched pair of Centers from a same district. Moreover, the patients will be from the Minhang district and the Changning district, two of a total of 13 districts in Shanghai, China. This may arouse concerns on the representation of the sample patients and extrapolation of our results to other patients. From a generalizability perspective, this study will recruit a diverse population across urban and rural Shanghai, and may be generalizable to other areas in China. Finally, given that Shanghai is one of the most economically developed large cities in China, whose residents have a relatively higher educational level, the results derived from our population may underestimate the effect of addressing health literacy and numeracy to improve self-management skills and glycemic control in Chinese diabetes patients. Nevertheless, it is plausible that the interventions, if effective in our population, would work in other populations.

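### The stated HbA1c analysis is at patient level, with no term for the eight randomized Centers or four matched pairs, and it conflicts with the power model, which also omits both.

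*Protocol article*

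**What the plan says.** **Design.** The Setting section states "A total of 800 diabetes patients will be recruited from eight Community Healthcare Centers", with five clinic sites per Center. The Randomization procedure section states "Randomization will occur at the level of the Community Healthcare Centers", four Centers to each arm. It continues: "We will then identify four matched pairs, with each pair consisting of two facilities with closest multivariable scores" and "Randomization will be performed within each pair, with one Center randomized to receive the intervention, and the other to the control condition". The Discussion adds that "we will ensure the matched pair of Centers from a same district", because usual care differs somewhat between the two districts.

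**Analysis.** The Statistical analyses section states "Analysis of covariance will be used to evaluate the improvement in HbA1c levels after adjusting for baseline values" and then "Multivariable general linear models will be used to additionally adjust for other baseline covariates including age, sex, and diagnosis date". The Abstract likewise says that intervention effects will be examined in multivariable general linear models. Neither place names a term for Center, site, provider or pair, a random effect, or a cluster-robust variance.

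**Power.** The Analytical power section simulates follow-up HbA1c from baseline, arm, a site effect, a provider effect and residual error, and gives 100.0% as the power of the analysis it proposes. It remarks that a simpler calculation would miss the two levels of clustering. It then reports a single-clustering check on 40 sites, also at 100.0%. No Center or pair effect appears, and no ICC is given.

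**The concern.** Patients are not randomized one by one; Centers are. Patients of one Center share staff, local practice and the Center's own HbA1c equipment, so their outcomes may be correlated. ANCOVA or a general linear model on patients, as named, treats all of them as independent. It can therefore read a chance difference between two sets of four Centers as an intervention effect, with a confidence interval that is too narrow.

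This is more than a detail left to an analysis plan. The article fixes the method, repeats the model class in the Abstract, and elsewhere assumes a different model for the same comparison. At stake are the primary HbA1c test, the secondary patient outcomes if they are analysed the same way, and the 95% confidence limits that the article uses as input ranges in the cost-effectiveness sensitivity analyses.

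**Working it through.** **Inputs from the protocol article.** 800 patients in 8 Centers (100 per Center); 5 sites per Center (40 sites); 30% loss, so 800 × 0.70 = 560 analysed, which is 280 per arm, 70 per Center and 14 per site; difference 0.8; SD 2.0 (survey SD 1.4); two-sided 5%.

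**Assumption.** The Center ICC. The article gives none, so a range is shown.

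**1. The stated power.** Ignoring clustering, SE = 2.0 × √(2/280) = 0.169 and 0.8/0.169 = 4.73. Power = Φ(4.73 − 1.96) = 99.7%; at SD 1.4 it exceeds 99.99%. With 40 sites of 14 as clusters and DE = 1 + 13 × ICC, power at SD 2.0 is 99.4%, 98.8% and 95.8% at site ICC 0.01, 0.02 and 0.05. So 100.0% is reproduced to within about 2 points for a site ICC up to about 0.03 (98.0%).

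**2. False-positive rate of the patient-level test.** With m = 70 per randomized Center, DE = 1 + 69 × ICC, and the true error is 2 × [1 − Φ(1.96/√DE)].

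| Residual Center ICC | DE | SE too small by factor | True error |
|---|---|---|---|
| 0.001 | 1.07 | 1.03 | 5.8% |
| 0.005 | 1.35 | 1.16 | 9.1% |
| 0.01 | 1.69 | 1.30 | 13.2% |
| 0.02 | 2.38 | 1.54 | 20.4% |
| 0.05 | 4.45 | 2.11 | 35.3% |

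The error reaches 10% at an ICC of about 0.006. Simulated patient-level ANCOVA (8 Centers × 70, four pairs, 5,000 null runs per setting) gave 13.4%, 20.2% and 36.1% at ICC 0.01, 0.02 and 0.05 with no gain from matching. When matching removed half of the Center variance it gave 9.7%, 14.0% and 24.4%.

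**3. Would the power section's clustering cure it?** No. With the variance at Center level and no gain from matching, simulation with the 40 sites as the clusters still gave about 11% to 26% over ICC 0.01 to 0.05. A t-test on Center means, or a paired t-test on the four pair differences, gave about 5% in the same settings.

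**4. Power at the randomized level.** SE = SD × √(2/280 × DE), with the noncentral t distribution on 8 − 2 = 6 df (Center means by arm) or 4 − 1 = 3 df (pair differences). No gain from matching or baseline adjustment is assumed.

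| Center ICC | SD 2.0: 6 df / 3 df | SD 1.4: 6 df / 3 df |
|---|---|---|
| 0.01 | 86% / 68% | 99% / 92% |
| 0.02 | 73% / 55% | 95% / 82% |
| 0.05 | 47% / 35% | 76% / 58% |

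**The case against.** The strongest reply is that the authors plainly know the trial is clustered. The Analytical power section models site and provider effects and presents the result as the power of the proposed analysis, so a mixed model may be intended and the Statistical analyses section merely condensed. This stands in part: a reader might infer that the plan ignores clustering outright, and the article does not support that. What it shows is two sections in conflict. Resolving the conflict in favour of the power section still leaves out Center and pair.

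Three other strong readings are tempting and unsupported.

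- **That the false-positive rate is known to be several times 5%.** No ICC is given. Below about 0.006 the rate is less than twice nominal, and matching on location, HbA1c and patient characteristics within district could lower it.
- **That adjustment is limited to age, sex and diagnosis date.** The wording introduces these as examples in an open list, on top of baseline HbA1c. Nor are the χ², t and Wilcoxon tests clearly part of the primary analysis; they can be read as descriptive comparisons.
- **That the imputation and the provider outcomes carry the same fault.** The article describes no imputation model and names no specific method for provider outcomes. Silence there is not an error.

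None of this removes the main point: any positive Center variance left after matching and baseline adjustment makes the stated standard errors too small.

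**Conclusion.** The point holds in conditional form. The named primary analysis does not respect the randomized unit, and it disagrees with the power model, which does not respect it either. The error of the nominal 5% test is about 13%, 20% and 35% at an assumed residual Center ICC of 0.01, 0.02 and 0.05 with 70 analysed per Center. If those ICCs apply before matching and matching removes half of the Center variance, it is about 10%, 14% and 24%. The direction follows from the design; the size rests on the assumed ICC.

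The same applies to the secondary patient outcomes if they are analysed alike, and to the confidence limits carried into the cost-effectiveness work. The stated 100.0% power is reproducible with sites as clusters but is not secure for eight Centers. This should be corrected before outcomes are analysed, because a positive HbA1c result could otherwise reflect differences between Centers.

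**What to change.** In the Statistical analyses section, prespecify one of the following for 12-month HbA1c:

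- a linear mixed model with baseline HbA1c, arm and district as fixed effects and random intercepts for Center and for site within Center; or
- an equivalent analysis of baseline-adjusted Center means.

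State whether the design factor is district or pair, and fix the degrees of freedom for the arm effect in advance: 8 − 1 (mean) − 1 (arm) − 1 (district) = 5, or 8 − 1 − 1 − 3 (pairs) = 3. Keep them even if the Center variance is estimated at zero. With eight Centers that estimate is zero or negative in about 26–29% of trials at ICC 0.01 and 13–17% at 0.02, and automatic degrees of freedom may then be far too large. A within-pair permutation test cannot serve as the primary test: with four pairs the smallest two-sided p is 2/2⁴ = 2/16 = 0.125.

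Include Center in the imputation model and use the same Center-level approach for the secondary outcomes. For provider outcomes use Center only, since two to four providers per Center across five sites cannot support a site term. Align the Analytical power section with the chosen model and restate the power for eight Centers with a stated ICC and its source.

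**Cost.** Revised text and a new power calculation. Confidence intervals become wider and the stated power less favourable. Recruitment and trial conduct are unchanged.
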